### Stage Two: Program Development

#### Objectives

This stage will take 12 months to complete and has the following objectives: (1) to organize the communities and form a partnership among these and members of academia under the principles of equity and mutual respect; (2) to define the priority problems related to the disabling effects of musculoskeletal diseases, and to identify possible solutions to these problems; and (3) to define the components of the csCBR program along with the necessary actions to implement them, assuring the necessary resources to execute them. This stage will follow a “qualitative dominant” methods perspective [42] being composed of three main and sequential activities: (1) community organization and partnership formation; (2) evidence assessment, merging, and summary; and (3) stakeholder deliberation. In addition, an anthropologist will conduct ethnographic work including nonparticipant observations and in-depth interviews on all these activities in order to produce a reflective-critical analysis from a medical anthropology perspective.

#### Community Organization and Partnership Formation

We will present the information gathered during the initial stage of this project to the community through the organization of community meetings at different strategic locations. During these meetings we will form 2 types of committees labeled as “first-level” or “second-level” committees. In Chankom, we will hold 11 meetings, one at each commissariat, and in the community-UHC-Nuevo León we will conduct 5 meetings, one at each of the health care units that form this center. These information meetings have the goal of creating awareness about the disabling effects of the musculoskeletal conditions explored within these communities. By the end of each meeting we will ask the community to choose 4 persons to constitute a first-level committee. A person from each of these first-level committees will participate in the second-level committee. There will be only one second-level committee, which includes representatives of all the strategic locations within our target communities (11 in Chankom and 5 in the community-UHC-Nuevo León).

The second-level committee of each community will be legally constituted as a “civil association”. This will be important for allocating and requesting financial resources, because in Mexico most government and nongovernment institutions can only serve organizations of this kind. The second-level committee will directly interact and work with representatives of the academic institutions involved in this project. During the first meeting of all committees, the members will define their roles as well as the rules for collaboration in relation to the processes of communication, decision making, and conflict resolution. We will use a nominal group technique, which is a group decision-making method, based on procedures for ideas’ exposition, discussion, and ranking that allows everyone’s opinion to be taken into account, reaching the best possible solution that is constituted by a mixture of all group members’ ideas [65].

The second-level committee and the academics will be in charge of all methodological and administrative decisions for the project, as they will take on the role of the principal investigator. All decisions taken within this partnership between communities and academia, from now on referred to as “the partnership”, will be the result of an ongoing analytic-interpretive-consensus process. In addition, the information and decisions generated within the partnership will be disseminated to the community via the first-level committees. In the same token, the community will be able to communicate with the second-level committee and academics through the first-level committees.

#### Evidence Assessment, Merging, and Summary

The first task for the partnership and the first-level committees will be to define the priority problems within their communities. The groups will use the knowledge generated during stage one of this project and the elements described by the WHO CBR matrix [41]. Priority problems refer to those issues that need to be urgently solved in order to decrease the disabling effects of musculoskeletal diseases at Chankom, and the community-UHC-Nuevo León. These issues will be organized and structured according to their main content in: (1) health, (2) education, (3) livelihood, (4) social, and (5) empowerment problems. The prioritization of problems will be based on their impact on the community’s health and physical function. We will then think about possible solutions using both, the communities’ social and cultural knowledge (local evidence) and the knowledge generated within the “scientific-academic” world (global evidence). These ideas will redefine community priority problems based on the cost, benefit, and efforts required to implement them.

The global evidence assessment will largely be the responsibility of the academic partners. This will be accomplished by combining the methodology for “overview of reviews” proposed by the Cochrane Collaboration [66] and the “evidence assessment” approach proposed by the “Grading of Recommendations Assessment, Development and Evaluation” group [67]. Once processed, this evidence will be formatted into a fourth grade level of comprehension, so every member of the partnership and committees can understand it. Following this, the partnership will merge both local and global evidences in order to construct a plan to solve the disabling problems posed by musculoskeletal diseases in the communities. Therefore, it is expected that this plan will be both solid, in relation to its scientific foundation, and sensitive to the cultural and social realities of each of the target communities.

Priority problems and the plan to attend them will be defined and written as an evidence brief (ie, a document that summarizes how the available evidence pertains to a pressing problem, select options for addressing the problem, and key implementation considerations). This evidence brief will be structured following the ideas developed by the McMaster Health Forum [68,69], along with ideas from the “scenario planning” strategy for organization planning [70]. These briefs will include: (1) a clear description of each problem including its context; (2) a description of possible individual, community, programmatic, and systemic solutions to address each problem through the use of different scenarios; (3) a description of expected outcomes (benefits, costs, and harms) for each scenario; (4) a simple description of the grade of uncertainty behind the expected outcomes of each scenario; (5) a description of possible barriers for the implementation of each possible solution; and (6) a clear description about the sources from which the information of the possible solutions and scenarios came.

#### Stakeholder Dialogue

The components of the csCBR program will be defined using the principles of the Communicative Action Theory, which assumes that communication aimed at reaching agreement is the base from which to coordinate the activities of social change [71]. Consequently, we will create a space for communication or forum to convene a stakeholder dialogue to support action for improving health outcomes through collective problem solving by different key decision makers. The stakeholder dialogue will be conducted based on the methods developed by the McMaster Health Forum [72]. In addition, we will attempt to achieve an “unforced consensus” [33], a goal not usually targeted by these kinds of forums. This consensus will be fundamental to assure the execution and sustainability of the csCBR program.

Key decision makers are defined as those knowledge users who are able to influence the decision-making processes of their respective areas. The partnership will identify key decision makers using the information gathered during the previous stage and substages of the project. We anticipate that identified key decision makers will represent at least one of the following areas: (1) traditional medicine, (2) professional health care, (3) government and nongovernment social welfare, and (4) health policy. During this part of the project we will intend to form an alliance with these key decision makers in order to create commitments that will ensure human and material resources for the execution of the csCBR program, independently from resources of this research project. We will recognize these key decision makers as “powerful allies”, based on the privileged position of power they held within their respective areas. Potential powerful allies will be invited to participate in the stakeholder dialogue through letters and person-to-person invitations.

The dialogue will be conducted over the course of several sessions in which participants will gather in a neutral, public location to talk about the information described in the evidence brief. A neutral facilitator, who will ensure a respectful and equitable communication among participants, will moderate the stakeholder dialogue. This facilitator will be responsible for all participants having the same chance to express their views during the dialogue. The final products from the stakeholder dialogue will include a dialogue summary (ie, a distillation of the key themes and insights that emerged during the dialogue) and the formation of a complex csCBR program composed by different components or actions along with a clear description of their respective expected outcomes. It is anticipated that these actions will include individual, community, and societal targets.

The components of the csCBR program will be defined through a nonforced consensus achieved through a process agreed on by all participants at the beginning of the dialogue. Once the dialogue is completed, the csCBR program will be written, and the resulting document will be shared with all participants in order to assure its fidelity in relation to what was agreed during the dialogue. Agreements with powerful allies will be confirmed and clinched by signing letters of commitment. This strategy aims to favor the long-term sustainability of the csCBR program within each targeted community.

### Stage Three: Program Implementation

This stage will be completed over 6 months following a “quantitative dominant” approach [42]. The stage involves conducting a pilot test of the CBR program developed during stage two, and the implementation of an improved CBR program in the two communities of interest. The pilot test will help in identifying barriers and facilitators for the program’s implementation, allowing corresponding program adjustments. All partnership members will contribute to the design, execution, and interpretation of the results of this stage.

We will choose 1 strategic site at each community (ie, 1 commissariat in Chankom and 1 health center of the UHC-Nuevo León) to implement the csCBR program designed during stage two of this protocol. An anthropologist will assess the operational aspects of the csCBR program using nonparticipant observations, informal interviews, in-depth interviews, and focus groups. This qualitative information will be used to design two questionnaires to evaluate the presence of facilitators and barriers for the implementation of each of the components of the csCBR program in the community. There will be one questionnaire designed for users of the program and another one for personnel involved in the program’s execution. Trained interviewers will apply the questionnaires to all participants of the pilot test through home visits, visits at jobsites, or telephone calls.

Qualitative data will be analyzed and interpreted by the anthropologist and some members of the partnership using content and thematic analysis techniques. This analysis then will be presented to all partners to decide the content of the questionnaires. We will use descriptive statistics to rank the frequency of facilitators and barriers observed during the pilot test. The partnership will use this information to make decisions about relevant changes to the original csCBR program and to elucidate implementation strategies aiming to improve its successful implementation in the community. Once changes have been made, we will proceed to implement the updated csCBR program in both communities.

### Stage Four: Program Evaluation

This stage will last for 18 months following a “pure mixed methods” approach [42] implying the simultaneous execution of quantitative and qualitative methods, each one producing results that will converge in a complete explanation of the researched phenomenon [73]. The objectives of this stage are: (1) to understand which components of the csCBR program are more effective, and what are their mechanisms of action; and (2) to evaluate the impact of the csCBR program on the functioning and quality of life (QoL) of the people living with musculoskeletal diseases in Chankom and the community-UHC-Nuevo León. This stage will allow us to get a complete explanation and understanding about the impact and mechanisms of action of the csCBR program developed.

Quantitative methods will consist of a longitudinal, prospective, and comparative pre/post intervention observational design. Qualitative data will be gathered through ethnographic fieldwork to understand the dynamics and mechanisms of action of each of the csCBR program components. The ethnographic work will also inform quantitative findings about the impact of the program on functioning and QoL.

The quantitative sampling strategies will vary between our two target communities. In Chankom, we will include all the people enrolled in the CBR program together with a sample of people with equivalent ethnic, cultural, and socioeconomic characteristics, who live outside Chankom and have not been exposed to the program (control population). In the community-UHC-Nuevo León, we will assemble a random probabilistic sample of people with musculoskeletal diseases who are involved in the CBR program, and an equal sample of people with osteoarthritis living in a community with similar socioeconomic and cultural characteristics as the community-UHC-Nuevo León, but that has not been in contact with the program (control population). Quantitative results of stage one will provide us with the information needed to calculate appropriate sample sizes. The ethnographic work will require purposeful sampling of people who participated in activities that were implemented in the CBR program for at least 3 months, in both target communities. This will assure that sufficient experience with the program’s processes and activities has been accumulated.

For the quantitative part, we will take baseline measurements, prior to the implementation of the program, and follow-up measurements every 6 months (4 measurements in total until 18 months) in both the target and control populations. Subjects of the control populations will be identified using the COPCORD screening methodology described in stage one of the project. We will measure: (1) 3 different tenses of physical function [53]; (2) QoL; and (3) outcomes related to each component of the csCBR program, whatever these may be.

As already mentioned, we anticipate that the csCBR program will include interventions at different levels, from the personal to the institutional level. In consequence, outcomes will be defined and measured according to the theoretical understanding of each level.

Hypothetical functioning will be measured through the WHO Disability Assessment Schedule 2 (WHODAS 2.0). The WHODAS 2.0 is a generic health-related disability assessment with excellent psychometric properties and was created through an extensive multicultural effort [74]. Experimental functioning will be evaluated using the 6MWT and the FDT. Both tests have shown excellent psychometric properties in musculoskeletal disease populations [57,59]. Enacted functioning will be measured subjectively through the Patient-Specific Functional Scale, which has shown excellent validity and reliability properties when applied in musculoskeletal-related pain populations [75], and semiobjectively using self-report, nonparticipant observations, and videos. QoL will be assessed through the WHO QoL Instrument. This instrument was developed through a multicultural collaboration and has been used with different populations, including older adults, showing excellent reliability and validity properties [76]. All questionnaires will be translated and culturally adapted to the Mayan language.

The ethnographic fieldwork will be conducted by a medical anthropologist and will include participant and nonparticipant observations, in-depth interviews, and focus groups. These qualitative methodologies will be conducted to understand the mechanisms of action of the different components of the program, along with their respective positive and negative aspects. In addition, the fieldwork data will help us in identifying relevant effects of the csCBR program, which can be measured quantitatively.

We will include descriptive and inferential statistic techniques to analyze the quantitative data. Inferential techniques will include multilevel modeling to explore effect modifiers on the outcomes of interest at different levels (eg, municipality, commissariat, or household levels), including between-group comparisons among target and control populations. We will use the statistical software STATA version 12. Ethnographic data will be analyzed following an analytic-interpretative-reflexive strategy from a medical anthropology perspective. These analyses will be further enriched by discussions with the partnership. All analytic and methodological decisions will be carefully registered in an audit trail. The results of this stage four will support decision-making processes within the partnership, allowing planning and conducting of a new situational analysis, thus completing the cyclical nature of the project (see Figure 1). The cyclical nature of this project implies that the csCBR program's components will be constantly refined, and the outcomes expected by their implementation will be obtained after the execution of several cycles.

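### At Nuevo León the programme sample covers all musculoskeletal diseases but the controls have osteoarthritis only, so participants with other diagnoses have no controls

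*Protocol article*

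**What the plan says.** The article's section Stage Four: Program Evaluation sets as its second objective "to evaluate the impact of the csCBR program on the functioning and quality of life (QoL) of the people living with musculoskeletal diseases" in both communities. The quantitative part is a "longitudinal, prospective, and comparative pre/post intervention observational design", with "follow-up measurements every 6 months (4 measurements in total until 18 months) in both the target and control populations".

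For Nuevo León one sentence defines both groups. On the programme side, "we will assemble a random probabilistic sample of people with musculoskeletal diseases who are involved in the CBR program". On the control side, "an equal sample of people with osteoarthritis living in a community with similar socioeconomic and cultural characteristics". The control community must resemble the target community socioeconomically and culturally and must not have met the programme. Nothing is said about diagnosis mix.

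The same section adds that "Subjects of the control populations will be identified using the COPCORD screening methodology described in stage one of the project". The analysis is to be multilevel modelling, including target-control comparisons. The article names no restriction, matching or adjustment by diagnosis.

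**The concern.** The evaluation is not randomised, so crediting a target-control difference to the programme depends on the controls showing how the same kind of people would have fared without it. Here the two groups are defined by different disease categories. Programme participants with back pain, rheumatoid arthritis or another non-osteoarthritis condition are compared with people who all have osteoarthritis. If these conditions run different courses over 18 months, part of the Nuevo León contrast reflects diagnosis and not the programme. The site's conclusion would also be stated for musculoskeletal diseases generally although its controls represent only one of them.

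**Working it through.** Stage four states no sample size, power or effect size (sample sizes await stage one), so there is no figure to reproduce. The check is a comparison of the definitions, followed by the algebra of what the design can identify.

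**1. Definitions side by side**

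| Item | Case definition | Section |
|---|---|---|
| Objective | Musculoskeletal diseases | Stage Four |
| Nuevo León programme sample | Musculoskeletal diseases | Stage Four |
| Nuevo León controls | Osteoarthritis | Stage Four |
| Chankom controls | No osteoarthritis restriction | Stage Four |
| COPCORD screening | Rheumatologic disorders generally | Stage One, Epidemiologic Study |

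The two terms are not used as synonyms. The Introduction (Musculoskeletal Diseases and Disability) lists osteoarthritis, back pain and rheumatoid arthritis as separate examples of chronic musculoskeletal disease. Osteoarthritis is thus a subset, and only the Nuevo León control definition is confined to it.

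**2. What the comparison can identify**

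Let T = 1 for programme and 0 for control, and N = 1 for non-osteoarthritis and 0 for osteoarthritis. Write mean 18-month change as

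change = a + b·T + g·N + h·T·N

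Here b is the programme effect in osteoarthritis, b + h is the effect in other diagnoses, and g is the difference in course between other diagnoses and osteoarthritis without the programme.

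- Programme, osteoarthritis: a + b
- Programme, other diagnoses: a + b + g + h
- Control, osteoarthritis: a
- Control, other diagnoses: no participants

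There are three observed means for four parameters. b is identified from the osteoarthritis cells. Only the sum g + h is identified, so the programme effect in other diagnoses cannot be separated from their natural course. A diagnosis term without the interaction gives an estimate of b, but that estimate comes from the osteoarthritis participants alone; applying it to other diagnoses assumes h = 0.

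**3. The unadjusted contrast**

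With q the non-osteoarthritis share of the programme sample:

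programme mean − control mean = (1 − q)(a + b) + q(a + b + g + h) − a = (b + q·h) + q·g

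The bracket is the average programme effect in the programme sample, and q·g is the bias. A fixed difference in level between diagnoses does not enter, because change from baseline is compared. Only a difference in course (g ≠ 0) matters.

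**4. How the bias behaves (assumed values only)**

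None of q, g or the group size is in the documents. Assume 200 per group, no programme effect, and a two-sided 5% test. The standard error is √(2/200) = 0.10 SD and the chance of a false positive is Φ(q·g/0.10 − 1.96) + Φ(−q·g/0.10 − 1.96).

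| q | g (SD) | Bias q·g (SD) | False-positive chance |
|---|---|---|---|
| any | 0 | 0 | 0.05 |
| 0.2 | 0.2 | 0.04 | 0.069 |
| 0.4 | 0.3 | 0.12 | 0.224 |
| 0.6 | 0.3 | 0.18 | 0.437 |

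The table shows that the consequence runs from negligible to serious over the assumed values. It is not an estimate for this study.

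**The case against.** The strongest reply is that this is a slip of wording. Osteoarthritis is the condition the Introduction highlights for Nuevo León and the one used to size the stage-one survey there, so the word may have been carried over. COPCORD screening would find other diagnoses anyway, and stage-four sample sizes are not yet set. It may equally be that osteoarthritis is the intended focus at that site. Both readings are possible, and the article does not settle between them. Either way the sentence has to change, because as written it would be followed by recruiting controls with one diagnosis for a programme group with several. A later analysis plan could restrict the contrast, but it could not supply controls who were never recruited.

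Two further parts of the reply stand. First, a reader might infer that the groups do not overlap at all and that no valid comparison is possible. The text does not support that: osteoarthritis falls within the programme group's definition, so a like-for-like comparison within osteoarthritis is available from the planned data. Second, baseline is measured in both populations, so differences in level between diagnoses (in walking distance or hand dexterity, for example) drop out when change is compared. Only diagnosis-specific courses remain as a source of bias.

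**Conclusion.** The inconsistency is real and nothing elsewhere in the article reconciles it. It concerns one site's quantitative target-control comparison; the Chankom control definition carries no osteoarthritis restriction. For Nuevo León participants without osteoarthritis, the design as written cannot distinguish programme effect from natural course.

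The size and direction of the bias cannot be derived. A reader might be tempted to take the non-osteoarthritis share from the article's prevalence figures: 10.5/26 = 0.40 or 17/26 = 0.65 for osteoarthritis, hence 35–60% without controls, and then to multiply by an assumed 0.2–0.3 SD to get a bias of 0.07–0.18 SD. The documents do not support this, for four reasons:

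- The 26% is the prevalence of musculoskeletal pain and not of diagnosed disease, so the quotient is not a share of cases.
- The second ratio sets a state numerator over a national denominator.
- The Epidemiologic Study section gives 20% osteoarthritis for Nuevo León, and the same arithmetic would then give 20/26 = 0.77, leaving 23%.
- The sample is drawn from people involved in a programme not yet designed, so its diagnosis mix is unknown. The 0.2–0.3 SD has no source in the documents.

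The conclusion therefore rests on the definitions and on the identification argument. It needs no assumed magnitude, only the premise that some programme participants will not have osteoarthritis.

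**What to change.** Use one case definition in both Nuevo León groups. In the stage-four sentence, define the controls as people with musculoskeletal diseases identified by the same COPCORD procedure as the programme participants, and make the comparison within diagnosis groups or adjusted for diagnosis group. The cost is more than a change of words, but small: some additional case confirmation, and recording of diagnosis, in the control community. The Results section says stage one had only just begun at Nuevo León, so the change can be made before stage-four controls are recruited. Matching on age and sex is optional and not part of this correction.

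If osteoarthritis-only controls are what is intended, keep them, restrict the Nuevo León target-control comparison to programme participants with osteoarthritis, and narrow that site's conclusion to osteoarthritis. This costs some precision, because part of the programme sample leaves the comparison, and some scope, because the objective for musculoskeletal diseases as a whole is then not answered by the controlled comparison at that site.

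Either change removes the q·g term as far as diagnosis group is concerned. Other confounding in a non-randomised comparison remains.
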